## Abstract

**Background:**

Ventricular tachycardia (VT) ablation in patients with ischemic cardiomyopathy (ICM) continues to be a challenging procedure with variable outcomes. Most current ablations are done using radiofrequency ablation (RFA). The new pulsed field ablation (PFA) technology may be able to achieve similar or superior procedural outcomes but potentially over shorter periods of time with less intravascular fluid infusion, but this possibility has never been tested.

**Objective:**

This study aimed to compare the procedural efficacy and safety of VT ablation in patients with ICM using focal PFA vs RFA catheters.

**Methods:**

This ASCEND-VT pilot study is a single-center trial randomizing patients to RFA vs PFA VT ablation in a 1:1 fashion. The new focal PFA catheter will be used under an investigational device exemption granted by the US Food and Drug Administration. Patients with mechanical valves will be excluded. The primary ablation target will be homogenization of endocardial late abnormal ventricular activity. Patients will be followed for 6 months after the procedure.

**Results:**

40 individuals will be randomized. The primary efficacy metric will be the ablation time needed to eliminate late abnormal ventricular activities in each patient. Additional efficacy and safety endpoints will be interrogated after the procedure and during outpatient follow-up.

**Conclusion:**

This is the first pilot randomized controlled trial comparing the safety and efficacy of focal PFA vs RFA VT ablation in ICM. Its results will inform the design of future larger studies that will further establish the clinical utility of PFA in the context of scar-related VT ablation.

Key Findings
▪ASCEND-VT is a pilot trial that randomizes patients with ischemic cardiomyopathy and ventricular tachycardia to endocardial ablation using standard radiofrequency vs novel pulsed field ablation catheter.▪The intervention arm will use the new FARAPOINT focal pulsed field ablation catheter (under the US Food and Drug Administration’s investigational device exemption).▪The immediate procedural endpoint in all patients will be total elimination of abnormal electrograms, specifically late abnormal ventricular activity (LAVA).▪The trial’s primary efficacy metric is the time needed to eliminate LAVAs in the 2 study arms. This will be tested for noninferiority.▪Additional efficacy and safety metrics will be assessed after the ablation and over the course of a 6-month follow-up period.

## Introduction

Ventricular tachycardia (VT) in the setting of ischemic cardiomyopathy (ICM) is a potentially life-threatening arrhythmia with a high rate of recurrence.^1^^,^^2^ Although implantable cardioverter-defibrillator (ICD) therapy can effectively interrupt VT and improve mortality,^3^^,^^4^ ICDs alone are often insufficient as long-term monotherapy in patients given the effect of ICD shocks on mortality, heart failure, and patient quality of life.^5^, ^6^, ^7^ Additional therapies for VT include antiarrhythmic medications (which can be ineffective and put patients at risk of adverse effects) and catheter ablation.^2^^,^^8^ Indeed, radiofrequency ablation (RFA) of VT has been proven to be effective in multiple clinical studies.^1^^,^^2^^,^^8^, ^9^, ^10^, ^11^, ^12^

The field of VT catheter ablation has evolved dramatically over the past several decades. However, the modern approach to VT ablation in patients with ICM relies heavily on substrate ablation targeting abnormal local delayed/fragmented electrograms (late abnormal ventricular activity [LAVA]) within the confines of the scar.^13^, ^14^, ^15^, ^16^, ^17^, ^18^ Indeed, successful elimination of LAVAs has been associated with improved VT-free survival.^14^^,^^15^ Unfortunately, substrate ablation using RFA is not always straightforward. Because RFA lesion formation is often inconsistent in scarred myocardium,^19^ abnormal potentials cannot be completely eliminated in a substantial proportion of patients.^15^^,^^20^ Furthermore, RFA substrate homogenization is frequently a lengthy procedure necessitating prolonged exposure to anesthetic agents and injection of substantial amounts of intravenous fluid via the open-irrigated RFA catheters.

Pulsed field ablation (PFA) is primarily a nonthermal ablation technique that causes cell death by creating pores in myocyte membranes.^21^^,^^22^ Although the nominal dimensions of the myocardial PFA lesions may be comparable with RFA, the former may be more efficient and consistent in creating lesions in scarred substrate.^23^, ^24^, ^25^ Just as importantly, in contrast to RFA, PFA lesions can be created much more rapidly (typically <10 seconds per site) and with the use of minimal or no irrigation. In contrast, the use of PFA may be associated with an increased risk of certain adverse events that are relatively specific to this technology; as shown in ablation studies targeting atrial arrhythmias, this includes the risk of coronary vasospasm and hemolysis-related acute kidney injury.^26^^,^^27^ Even so, the recently published aggregate ADVANTAGE AF data suggest that the overall safety profile for atrial PFA ablations is very favorable (primary safety endpoint rate 2.0%; myocardial infarction rate 0.2%; and clinically relevant hemolysis rate 0.6%, although no events required hemodialysis).^28^

Several small studies and case reports have examined the safety and efficacy of PFA in the context of VT ablation.^29^, ^30^, ^31^, ^32^, ^33^, ^34^ Larger cohort data on PFA ablation of VT and premature ventricular contractions have only been published recently. This includes our own experience with a large-footprint pentaspline PFA catheter (n = 11)^35^ and a larger series by Ruwald et al^36^ (n = 35) that relied on a focal ablation catheter and PFA generator. The outcomes in VT ablation were similar to what was previously reported with focal RFA catheters. In particular, Ruwald et al^36^ saw a 55% 1-year recurrence rate in VT ablation patients. However, it is important to state that the studied population was enriched for high-complexity cases with intricate, nonischemic substrate. Although the complication rates in these (and other) studies are reassuring,^35^, ^36^, ^37^ the safety of PFA is yet to be confirmed in a more uniform population.

Therefore, we have designed a randomized pilot study intended to directly compare the safety and efficacy of PFA vs standard RFA using a prespecified procedural endpoint (elimination of abnormal potentials) in patients with ICM and VT. We hypothesize that the time needed to eliminate the abnormal potentials will be shorter with PFA than with RFA. We will use the new focal FARAPOINT PFA catheter that has similar dimensions and handling to the existing RFA catheters.

## Methods

The ASCEND-VT trial is a single-center, randomized noninferiority pilot study comparing the efficacy and safety of the novel FARAPOINT PFA catheter vs standard RFA catheters during ablation of VT in patients with ICM. The study conforms to the Declaration of Helsinki. It has been approved by the Cleveland Clinic Internal Review Board and the US Food and Drug Administration, which granted an investigational device exception (G220079). The trial is listed in the ClinicalTrials.gov registry (NCT06891456). The study is investigator initiated and represents collaborative research between Cleveland Clinic and Boston Scientific Corporation. It is funded by Boston Scientific Corporation. Given that this is a trial design manuscript, there are no primary data available for sharing.

### Trial design

A total of 40 patients (up to 50 patients will be screened) with ICM and VT will be randomized to PFA vs RFA for VT ablation in a 1:1 fashion using a block-randomization design (block size = 4). Follow-up will be 6 months. The total enrollment period is anticipated to be 12 months.

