### Eligibility

Inclusion and exclusion criteria are presented in Table 1. Briefly, eligible patients must have a documented history of sustained monomorphic VT in the setting of ICM with a left ventricular ejection fraction (LVEF) of ≥20%. Important exclusion criteria include the presence of mechanical valves or a left ventricular (LV) assist device; patients with suspected epicardial substrate will also be excluded. Potential participants will be identified and approached in outpatient electrophysiology clinics or in the inpatient setting. After reviewing a study information sheet, discussing the study with the research coordinator, and having all their questions addressed, interested subjects will provide a written informed consent before enrolling in the study.

**Table 1 tbl1:** Study inclusion and exclusion criteria

Inclusion criteria		Exclusion criteria
Age ≥18 y		Unable to provide an informed consent
Ischemic heart disease with previous myocardial infarction		Idiopathic VT
LVEF ≥20% estimated by TTE within 90 d before enrollment		Mobile LV thrombus
Documented sustained monomorphic VT with any of the following characteristics:		Acute coronary syndrome within the preceding 2 mo (if incessant VT ≥1 mo before enrollment)
	≥2 documented episodes in patients with ICD	Comorbidity likely to limit survival to <12 mo
	≥1 documented episode in patients without ICD	New York Heart Association class IV heart failure
	Recurrent VT despite antiarrhythmic medications (ineffective, contraindicated, or not tolerated) or ICD interventions	Estimated glomerular filtration rate <30 mL/min/1.73 m^2^
Provision of a signed and dated informed consent form		Thrombocytopenia or coagulopathy
Stated willingness to comply with all study procedures and availability for the duration of the study		Contraindication to heparin
		Pregnancy or lactation
		Cardiac surgery within the past 2 mo
		Active infection
		Clinical, laboratory, or imaging evidence of active ischemia
		Severe left heart valvular heart disease (aortic/mitral stenosis or regurgitation)
		Any concomitant congenital heart disease
		Previous catheter or surgical ablation of VT within the past 2 mo
		Anticipated need for epicardial mapping and ablation
		For individuals with no preexisting ICD: ineligibility for an ICD implant
		Preexisting LVAD or other hemodynamic assist device
		Present mechanical heart valve
		Cardiogenic shock unless it is caused by incessant VT

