### Ablation procedure: Substrate mapping

In the control arm, the choice of mapping system and mapping catheters will depend on the operator’s discretion using a commercially available electroanatomic mapping system and mapping catheter. In the intervention arm, mapping will be done using the OPAL HDx mapping system (Boston Scientific, Marlborough, MA) along with the ORION multipolar basket catheter (Boston Scientific). Ablation catheters (outlined below) may also be used for mapping in all patients.

In both study arms, substrate mapping will be done during sinus rhythm and/or paced rhythm.

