### Ablation procedure: Substrate ablation

All LAVA areas will be targeted for ablation unless concern for collateral damage is thought to outweigh the benefits by the operator (eg, vicinity of conduction system). Ablation should not be performed in the proximity of metallic devices (such as intracardiac lead electrodes) to avoid arcing, cardiac trauma, and/or damage to the devices.

In the control arm, ablation will be done using commercially available contemporary RFA contact force–sensing slow-flow irrigated RFA catheters using standard irrigation settings and 30–50 W output for at least 30 seconds. The goal of each lesion will be the complete elimination of LAVA and/or local myocardial noncapture during high-output pacing (10 mA/2 ms to 20 mA/2 ms).

In the intervention arm, PFA will be done via the FARAPOINT focal catheter (Boston Scientific) using 5 bipolar/biphasic trains of 2.0 kV applications delivered over 2.5 seconds; the number of applications will be repeated based on lesion depth needs. There will be no limit on the number of RFA or PFA lesions.

In both study arms, the ablated areas will be remapped using the same catheter used for baseline substrate mapping and elimination of LAVAs will be confirmed by the primary operator (post hoc data review by the principal investigators [[name] and [name]] to confirm LAVA elimination will also be performed, and any discrepancies will be documented). In addition, high-output pacing (10 mA/2 ms to 20 mA/2 ms) will be delivered to the ablated sites to confirm noncapture at high or very high output. If persistent LAVAs and/or locations with persistent myocardial capture are identified, additional ablation is encouraged in both study arms.

Patients with an anticipated need for epicardial access will be excluded from the study. However, in cases where ad hoc epicardial access becomes necessary in an enrolled study subject (eg, unexpected identification of an epicardial VT focus during the procedure), epicardial mapping/ablation can be performed as clinically necessary; however, only RFA ablation is permitted in the pericardial space (or inside the coronary sinus system).

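### A single published block size of 4 in a one-center, unblindable trial makes on average one third of allocations deducible in advance, an avoidable risk of selection bias

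*Protocol article*

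**What the plan says.** Under Trial design, the article plans "A total of 40 patients (up to 50 patients will be screened"), who "will be randomized to PFA vs RFA for VT ablation in a 1:1 fashion", "using a block-randomization design (block size = 4"). One block size is given. Neither varying sizes nor stratification is mentioned. The opening of Methods states "The ASCEND-VT trial is a single-center, randomized noninferiority pilot study".

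The arms can be told apart in the procedure room. Under Substrate mapping: "In the intervention arm, mapping will be done using the OPAL HDx mapping system", while the control arm uses whichever commercial system the operator prefers. Under Substrate ablation: "In the control arm, ablation will be done using commercially available contemporary RFA contact force", against the focal PFA catheter in the other arm. The Discussion confirms that mapping systems and mapping catheters differ by arm.

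Entry involves judgement. One exclusion in Table 1 is "Anticipated need for epicardial mapping and ablation". Table 2 places screening, enrollment and baseline anywhere from day −90 to day −1.

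The primary endpoint, time to eliminate all targeted LAVAs, is compared by a two-sample t test (Statistical analysis and power calculations). The Discussion adds a further analysis that scales this time by the LAVA area at baseline.

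**The concern.** Randomization prevents selection bias only if those who enroll patients cannot tell which arm comes next. With a known fixed block, the end of each block follows from its beginning. Hiding the list does not help when past allocations are visible and the block size is published. At a single center, one team can follow the whole sequence.

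A person who knows the next arm could, without intending to, judge a borderline epicardial question differently or bring a patient forward or defer one. If the patients entered under known assignments differ in how much ablation they need, the arms differ at baseline, and an unadjusted t test carries that difference into the primary result. With 40 patients, a baseline comparison could not reliably reveal it.

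**Working it through.** **Inputs.** Block size 4, ratio 1:1, 40 randomized and one center (Trial design; Methods). Minimum enrollment 36, 10% withdrawal, significance level 0.05, power 80% (Statistical analysis and power calculations). The article gives no predictability figure.

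**The plan's own number.** 36 / (1 − 0.10) = 40, as stated. With one unstratified list this makes 40 / 4 = 10 complete blocks.

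**Assignments known with certainty.** A 1:1 block of 4 has 6 equally likely sequences. An assignment is certain once one arm's two places are used.
- Positions 1 and 2: never certain.
- Position 3: certain if the first two match, which is 2 of 6 sequences, so 1/3.
- Position 4: always certain.

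Expected fraction = (0 + 0 + 1/3 + 1) / 4 = 1/3. Over 40 patients this is 40/3 = 13.3. Each block contributes 1 certain assignment (probability 2/3) or 2 (probability 1/3), so the variance per block is 2/9 and the SD over 10 blocks is √(20/9) = 1.5. The total lies between 10 and 20, with a central 95% range of 11 to 16.

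**Best guess.** Guessing the arm that is behind is right with probability 1/2, 2/3, 2/3 and 1 at positions 1 to 4. The mean is (1/2 + 2/3 + 2/3 + 1) / 4 = 17/24 = 70.8%, against 50% under simple randomization.

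**Alternatives.** Fixed blocks were enumerated exactly. Varying blocks were simulated with 2,000 lists of 40, each size equally likely. The simulated observer knows the past allocations and the set of sizes, but not their order.

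| Scheme | Certain | Best guess correct |
|---|---|---|
| Fixed 4 | 33.3% | 70.8% |
| Fixed 6 | 25.0% | 68.3% |
| Fixed 8 | 20.0% | 66.6% |
| Random 4/6 | 5.8% | 68.9% |
| Random 4/6/8 | 2.4% | 67.7% |

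For a random 4/6 mix, 0.058 × 40 gives about 2 certain assignments instead of 13.

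**Possible size of bias.** The documents give no figure for steering, so this is an assumption shown as a range. Suppose every certain PFA assignment goes to a patient easier by s, and every certain RFA assignment to a patient harder by s, in SD units of the endpoint. One third of each arm shifts, so the difference moves by (2/3)s. For s = 0.25 to 0.5 this is 0.17 to 0.33 SD. For scale, 18 per arm with 80% power and a two-sided 0.05 t test (sidedness is not stated) implies a detectable difference of about 0.96 SD.

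**Imbalance under a 4/6 mix.** At 40 patients, an even number remains in any unfinished block (2 of 4, 2 of 6 or 4 of 6), so the arms differ by at most 2. Stopping at an odd total could leave 3 of 6, a difference of up to 3.

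**The case against.** The strongest reply is that predictability is not bias.

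- **Tracking is needed.** The one-third figure applies to someone who follows allocations in randomization order. The article does not say when in the 90-day window randomization falls. If it happens well before the procedure, a tally built from procedures may be out of order. The text also suggests more than one operator. A reader might infer that all staff see every allocation, but the article does not say so. What stands is that a coordinator or a close-knit team could keep the tally.
- **Room to steer is limited.** Only 10 spare patients may be screened, some patients are inpatients, and recurrent VT limits deferral. LAVA extent is mapped during the procedure, so its burden must be guessed beforehand, and epicardial need does not measure endocardial extent. This makes steering harder but does not exclude it.
- **A safeguard exists.** Scaling time by baseline LAVA area addresses one route by which patient mix could matter. It is an additional analysis, however, and would offset the risk only partly. A reader might also assume that elimination time depends mainly on scar extent. The article does not state this, and the point does not need it.
- **Concealment may be described elsewhere.** A journal article can leave it to the full protocol, so its absence here is no finding. Even perfect central concealment leaves deduction from a known fixed block intact.
- **The remedy is partial.** Varying blocks hardly change best-guess accuracy (71% to 69%). This is correct, and the case for the change rests on the certain assignments.

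**Conclusion.** The point holds as an avoidable risk. On average 33% of assignments (about 13 of 40; range 10 to 20) can be known beforehand by anyone who knows the block size and has followed earlier allocations in order. This assumes complete blocks of 4 and a single list. Stratification, if there is any, would leave the fraction within complete blocks unchanged but would require tracking by stratum.

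A reader might conclude that the trial is biased in favor of PFA. The documents do not support that: nothing shows that allocations were anticipated or entry steered, and the 0.17 to 0.33 SD above is an illustration on assumed steering. What they do support is that the stated block design gives weaker protection than it could, in a trial whose operators cannot be blinded, whose entry involves judgement and whose primary test is unadjusted.

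**What to change.** For patients not yet randomized, replace the fixed block of 4 with a computer-generated list of randomly varying block sizes, for example 4 and 6, and do not disclose the sizes to enrolling staff. State in the report when the change took effect.

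Certain assignments fall from about 33% to about 6%, and best-guess accuracy from about 71% to 69%, so the change should not be presented as making allocation unguessable.

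Cost: a new list, and possibly a minor amendment to the ethics-board and investigational-device approvals. Final arm sizes could differ by up to 2 at 40 patients, or 3 if enrollment stops at an odd number.

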### Eligibility

Inclusion and exclusion criteria are presented in Table 1. Briefly, eligible patients must have a documented history of sustained monomorphic VT in the setting of ICM with a left ventricular ejection fraction (LVEF) of ≥20%. Important exclusion criteria include the presence of mechanical valves or a left ventricular (LV) assist device; patients with suspected epicardial substrate will also be excluded. Potential participants will be identified and approached in outpatient electrophysiology clinics or in the inpatient setting. After reviewing a study information sheet, discussing the study with the research coordinator, and having all their questions addressed, interested subjects will provide a written informed consent before enrolling in the study.

**Table 1 tbl1:** Study inclusion and exclusion criteria

Inclusion criteria		Exclusion criteria
Age ≥18 y		Unable to provide an informed consent
Ischemic heart disease with previous myocardial infarction		Idiopathic VT
LVEF ≥20% estimated by TTE within 90 d before enrollment		Mobile LV thrombus
Documented sustained monomorphic VT with any of the following characteristics:		Acute coronary syndrome within the preceding 2 mo (if incessant VT ≥1 mo before enrollment)
	≥2 documented episodes in patients with ICD	Comorbidity likely to limit survival to <12 mo
	≥1 documented episode in patients without ICD	New York Heart Association class IV heart failure
	Recurrent VT despite antiarrhythmic medications (ineffective, contraindicated, or not tolerated) or ICD interventions	Estimated glomerular filtration rate <30 mL/min/1.73 m^2^
Provision of a signed and dated informed consent form		Thrombocytopenia or coagulopathy
Stated willingness to comply with all study procedures and availability for the duration of the study		Contraindication to heparin
		Pregnancy or lactation
		Cardiac surgery within the past 2 mo
		Active infection
		Clinical, laboratory, or imaging evidence of active ischemia
		Severe left heart valvular heart disease (aortic/mitral stenosis or regurgitation)
		Any concomitant congenital heart disease
		Previous catheter or surgical ablation of VT within the past 2 mo
		Anticipated need for epicardial mapping and ablation
		For individuals with no preexisting ICD: ineligibility for an ICD implant
		Preexisting LVAD or other hemodynamic assist device
		Present mechanical heart valve
		Cardiogenic shock unless it is caused by incessant VT

ICD = implantable cardioverter-defibrillator; LV = left ventricle; LVAD = left ventricular assist device; LVEF = left ventricular ejection fraction; MI = myocardial infarction; TTE = transthoracic echocardiogram; VT = ventricular tachycardia.

The study protocol and follow-up plan are presented in Figure 1.

